**Secondary Outcomes**
The frequency of patient discharges from the Emergency Department in a sinus rhythm [Time Frame: From the drug initiation and for 6 h] The frequency of successful cardioversion to sinus rhythm [Time Frame: From the drug initiation and for 24 h, 24 h ECG Holter monitoring] The time until the cardioversion to sinus rhythm [Time Frame: From the drug initiation and for 6 h] The frequency of electrical cardioversion [Time Frame: From the drug initiation and for 24 h] The frequency of arrhythmias: burden of PVCs, NSVT episodes, SVT episodes [Time Frame: From the drug initiation and for 24 h] The frequency, severity and type of Adverse Events [Time Frame: From the drug initiation and for 30 days]

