## 2. Objectives

The primary goals of this clinical trial are to prove the superiority of flecainide over amiodarone in the successful cardioversion of paroxysmal atrial fibrillation at the Emergency Department and to prove that the safety of flecainide is non-inferior to amiodarone in patients with coronary artery disease without residual ischemia and an ejection fraction over 35%. The secondary goals of the study are to prove the superiority of flecainide over amiodarone in the reduction in hospitalizations from the Emergency Department due to atrial fibrillation in the time taken to achieve cardioversion, and in the reduction in the need to conduct electrical cardioversion. A successful cardioversion is defined as the restoration of the sinus rhythm, documented by a 12 lead ECG lasting at least 1 h. 

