#### 3.5.2. Intervention Visit (V0)

The intervention visit is defined as the time at which the study staff intravenously administers the assigned drug and coincides with the screening visit. The drug that will be administered to each patient will be determined randomly, through a simple randomization process, as detailed in the relevant section. Patients in both groups will remain at the ED for a total of 6 h after starting the treatment, regardless of cardioversion status. If no adverse events occur during this time, including an AV block, sinus bradycardia < 50 bpm, syncope, presyncope, or systolic blood pressure < 90 mmHg and a cardioversion to sinus rhythm is successful, the patient will be discharged. Otherwise, the patient will be admitted to the hospital. Patients receiving flecainide with an unsuccessful cardioversion at 6 h will be hospitalized and receive amiodarone. Patients with an unsuccessful drug cardioversion after 24 h will undergo electrical cardioversion, according to the clinical judgment of the attending physician. All patients (i.e., those who were discharged at 6 h following a successful cardioversion and those who were hospitalized) will be under continuous 24 h ECG halter monitoring. The hospitalized patients will also be under continuous ECG monitoring until the time of a cardioversion. The 24 h ECG halter will be removed at 24 h from drug administration initiation, regardless of the cardioversion status.

In case of hemodynamic instability during or after the administration of the drug, or if the Δ (troponin at 1 h) is above the limit of the hospital’s laboratory troponin cut-off levels, the administration of the drug will cease, and the patient will be treated according to the guidelines. At discharge, the administration or non-administration of other medication will follow the guidelines, with the exception that patients will not receive treatment with a class Ic antiarrhythmic agent. 

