### 3.6. Interventions

Individuals randomized to the flecainide arm will intravenously receive flecainide at a dose of 2.0 mg/kg (maximum dose of 150 mg) throughout the 10 min in the emergency department. Flecainide will be dissolved in a 100 mL D/W 5% solution.

Patients randomized to the amiodarone arm will intravenously receive amiodarone at a dose of 5.0–7.0 mg/kg over 1 h in the emergency department, as well as a follow-up dose of 50 mg/h (a maximum dose of 1000 mg) for up to 24 h (Figure 2). 

Intravenous metoprolol is administered in patients with atrial fibrillation exhibiting a ventricular rate over 100 bpm, according to a physician’s decision. 

Hemodynamically stable patients with an unsuccessful pharmacological cardioversion at 24 h will undergo electrical cardioversion, according to the clinical judgement of the treating physician.

Any prior use of an antiarrhythmic agent will be documented in the case report form (CRF) and all concomitant medications or other therapies will also be documented. For patients withdrawing from the study, the reasons and any follow-on therapy are to be documented in the CRF.

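### The 24-hour window for counting electrical cardioversion closes just as the scheduled procedure becomes due, so the endpoint misses essentially all procedures done for drug failure

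*Protocol article*

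**What the plan says.** Section 2 (Objectives) lists superiority of flecainide "in the reduction in the need to conduct electrical cardioversion" among the secondary goals. The endpoint that serves this goal is in Table 3: "The frequency of electrical cardioversion [Time Frame: From the drug initiation and for 24 h".

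Two sections say when the procedure is planned:

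- Section 3.5.2: "Patients with an unsuccessful drug cardioversion after 24 h will undergo electrical cardioversion, according to the clinical judgment of the attending physician".
- Section 3.6: "Hemodynamically stable patients with an unsuccessful pharmacological cardioversion at 24 h will undergo electrical cardioversion", again by the treating physician's judgment.

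Section 3.6 also lets the amiodarone infusion run for up to 24 h. Section 3.5.2 provides that a patient who becomes hemodynamically unstable during or after the drug stops it and is treated according to guidelines. Electrical cardioversion is neither named nor ruled out there. Follow-up runs to 30 days (section 3.5.3), and Table 2 marks an endpoint assessment at the 30-day call.

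**The concern.** An endpoint meant to show that one drug spares patients a procedure has to be open when the procedure is planned. Here the counting period ends at the point where drug failure is established and the procedure follows. What stays inside the window is mainly the unscheduled procedure, which reflects instability more than failure to convert.

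Two misreadings could follow. A finding of no difference could arise because the clock stopped too soon. A difference, if one appeared, could be read as efficacy when it reflects tolerability. A procedure close to 24 h might also fall in or out of the count for logistical reasons. That is undesirable in an open-label trial where the procedure is left to clinical judgment.

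**Working it through.** **Step 1. Set the times side by side.**

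| Source | Time from drug initiation |
|---|---|
| Table 3, counting window | 0 to 24 h |
| Section 3.5.2, scheduled procedure | after 24 h |
| Section 3.6, scheduled procedure (stable patients) | at 24 h |
| Section 3.5.2, guideline treatment of instability | any time during or after the drug |

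Under section 3.5.2, no scheduled procedure falls inside the window in either arm. Under section 3.6, 24 h is when failure is judged and the procedure follows, so at most it ties with the boundary. Only the last row leads to a clearly countable procedure.

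**Step 2. Check the formula on the plan's own figure.** The plan gives no calculation for this endpoint. Its only sample-size figure (section 3.4) is 96 per arm, from 65% and 45%, 80% power and type I error 0.05. The usual two-proportion formula, two-sided, without continuity correction, is

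n = [1.960·√(2·p̄·(1−p̄)) + 0.842·√(p₁(1−p₁) + p₂(1−p₂))]² / (p₁−p₂)²

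With p̄ = 0.55: [1.960·√0.495 + 0.842·√0.475]² / 0.04 ≈ 3.838/0.04 ≈ 96. It reproduces. That figure has no bearing on the present point; the match only shows that the formula is a fair tool for the illustrations below.

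**Step 3. What the present window could detect.** The documents give no rate of early electrical cardioversion, so let u be an assumed rate, the same in both arms of 100. Expected events per arm are 100u, and the chance of none in the whole trial is (1−u)²⁰⁰.

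| Assumed u | Expected per arm | Chance of no event in 200 |
|---|---|---|
| 0% | 0 | 100% |
| 1% | 1 | 13% |
| 2% | 2 | 1.8% |
| 5% | 5 | under 0.01% |

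Power with n = 100 per arm is Φ{[|p₁−p₂| − 1.960·√(2p̄(1−p̄)/n)] / √[(p₁(1−p₁)+p₂(1−p₂))/n]}. For assumed in-window rates of 1% v 2%, 2% v 5% and 1% v 5% it gives 8%, 21% and 38%. The normal approximation is rough at such small counts.

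**Step 4. What a window covering the scheduled procedure could detect.** The documents give no 24-h failure rate either; section 3.4 quotes pooled 4-h conversion rates only. The rates below are assumptions, and every failure is taken to be cardioverted.

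| Assumed failure at 24 h, flecainide v amiodarone | Power, 100 per arm |
|---|---|
| 10% v 20% | 51% |
| 15% v 30% | 72% |
| 20% v 40% | 88% |

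For the first row: p̄ = 0.15, √(2·0.15·0.85/100) = 0.0505, √((0.09+0.16)/100) = 0.05, and Φ{(0.10 − 0.0990)/0.05} = Φ(0.02) ≈ 0.51.

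If only half of the failures in each arm were cardioverted, 20% v 40% would shrink to 10% v 20%, and power would drop from 88% to 51%.

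**The case against.** **The endpoint is not empty.** A reader might infer from the timings that no event can be counted. The documents do not support that. Section 3.6 says at 24 h, not after it, and limits its rule to stable patients. Section 3.5.2 allows guideline treatment of instability at any time, so earlier procedures can occur and would count. This objection stands. The fault is that the window counts mainly the wrong procedures.

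**The discharge endpoint does not share the fault.** It has a 6-h window, and section 3.5.2 says "Patients in both groups will remain at the ED for a total of" 6 h, so a reader might infer that discharge also falls outside its window. But the same section describes converted patients as discharged at 6 h. The outcome is settled when that window closes.

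**Much of the information survives elsewhere.** Table 3 also lists conversion to sinus rhythm within 24 h, and patients who fail it are largely the candidates for the procedure. This stands in part. It reduces the loss, but failure to convert is not the same as undergoing the procedure, and Section 2 states its goal in terms of the procedure.

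**The illustrated gain is assumed.** This also stands. The procedure is left to clinical judgment, and flecainide failures receive amiodarone from 6 h, which may narrow the difference between arms by 24 h. The power figures show that the endpoint could carry information, not how much it will.

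**The endpoint is minor.** It is one of six secondary outcomes and is not among the two that section 3.7 calls main. That bears on severity, not on whether the mismatch exists.

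**Conclusion.** The point holds as a mismatch between Table 3 and sections 3.5.2 and 3.6. As written, the endpoint excludes essentially all protocol-scheduled electrical cardioversions, apart from a possible tie at exactly 24 h. It leaves mainly unscheduled ones to test a named secondary goal. That conclusion rests on the documents' own timings and needs no assumed rate.

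The size does rest on assumptions: about 8% to 38% power for the in-window contrasts tried, against 51% to 88% if the scheduled procedures were counted and every failure were cardioverted. Neither range is a forecast.

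The primary endpoints and the sample size are unaffected. This is a moderate correction to one secondary endpoint.

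**What to change.** Reconcile Table 3 with sections 3.5.2 and 3.6, and extend the counting window to cover the scheduled procedure. One workable definition is any electrical cardioversion from drug initiation to the end of the index hospital stay. If day 30 is preferred, report procedures for later recurrent AF separately, because they are not failures of the index treatment. Sections 3.5.2 and 3.6 should also agree on whether the planned time is at or after 24 h. Which of the two is clinically right is not a matter for this review.

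The cost is small. Follow-up and endpoint assessment already extend to 30 days, but the documents do not show that procedures after 24 h are specifically recorded. The case report form therefore needs an entry for each one, with its time and reason. The change affects counting only and should be made before results are compared by arm.

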#### 3.5.3. Follow-Up Phase (from Intervention Visit to 1 Month)

The follow-up of the enrolled subjects will commence from the intervention visit and will extend to 30 days at the common study termination date.

At 24 h, patients will visit the investigation site for a clinical evaluation, including a physical examination, ECG and echocardiography, the removal of the 24 h ECG halter device and an adverse events assessment. 

At 30 days, a phone-driven follow-up evaluation is conducted for the assessment of any of the study’s outcomes and adverse events (AE). Patients will also be instructed to report earlier to the study center if they have symptoms suggestive of an AE. 

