### 3.7. Outcomes

The study’s primary endpoints are the frequencies of successful cardioversion within 6 h of drug administration as well as the combined frequency of PVCs, NSVT, SVT, bradycardia and hypotension during the same time frame. The main secondary endpoints are the frequency of patient discharges from the Emergency Department with a sinus rhythm and the frequency of successful cardioversion to a sinus rhythm within 24 h. All adverse effects, including extracardiac, will be assessed and categorized based on their severity, type and frequency. Table 3 lists all the study primary and secondary endpoints.

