Furthermore, we undertook the decision to place a 24 h ECG halter device monitor, on top of the 6 h ECG monitoring at the ED, to ensure the timely detection of any adverse event that would otherwise be missed, such as PVCs, NSVT, SVT or bradycardia. As for the decision to discharge hemodynamically stable patients that have been cardioversed at 6 h, this was based on the recommendations by Dan et al. that continuous medical supervision and ECG monitoring during drug infusion and afterwards for at least half of the drug half-life is needed. Based on this, we opted to not monitor the discharged patients by other means, except from the halter device. These measures were deemed as acceptable by the National Organization for Medicines and National Ethical Committee during the approval process of this trial. 

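### Between 6 h and about 24 h, how closely patients are observed depends on conversion and on freedom from early events, so the single 30-day adverse-event frequency is liable to unequal detection between arms

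*Protocol article*

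**What the plan says.** **Outcome.** The last secondary outcome in Table 3 is "The frequency, severity and type of Adverse Events [Time Frame: From the drug initiation and for 30 days". Section 3.7 makes it broad: "All adverse effects, including extracardiac, will be assessed and categorized based on their severity, type and frequency". Section 3.8 bases the safety assessment on adverse-event reports from consent to the final visit, without separating periods or sources of detection.

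**0 to 6 h.** Section 3.5.2: "Patients in both groups will remain at the ED for a total of 6 h after starting the treatment, regardless of cardioversion status".

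**At 6 h.** If no adverse event has occurred (the section names several, including hypotension and bradycardia) and "a cardioversion to sinus rhythm is successful, the patient will be discharged. Otherwise, the patient will be admitted to the hospital".

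**6 to 24 h.** For admitted patients, section 3.5.2 adds: "The hospitalized patients will also be under continuous ECG monitoring until the time of a cardioversion". For discharged patients, the Discussion says "we opted to not monitor the discharged patients by other means, except from the halter device". Everyone keeps the Holter: "The 24 h ECG halter will be removed at 24 h from drug administration initiation, regardless of the cardioversion status".

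**24 h and 30 days.** Section 3.5.3: "At 24 h, patients will visit the investigation site for a clinical evaluation, including a physical examination, ECG and echocardiography". That visit also includes an adverse-event assessment. A telephone assessment follows at 30 days, and patients are told to report symptoms sooner. Table 2 schedules both contacts for all patients.

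**The concern.** The setting in which a patient is observed after 6 h is decided after randomisation, partly by conversion. Conversion is a primary efficacy outcome, and section 3.4 cites pooled rates of 65% for flecainide and 23% for amiodarone within 4 h. More flecainide patients should therefore be at home. A Holter records rhythm. It does not record blood pressure, and it does not replace staff who see and write down minor or extracardiac events. The trial is also open-label.

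Analysing patients as randomised does not remove this, because the imbalance lies in how events are found and not in who is counted. At stake is the interpretation of a secondary outcome. A lower adverse-event frequency on flecainide could partly reflect fewer patients in a hospital bed, and it would be read as support for the drug's safety.

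**Working it through.** **The plan's own figures.** The document gives no figure for the 30-day adverse-event comparison. Its sample size of 96 per arm reproduces exactly as 65% versus 45%, two-sided 0.05, 80% power, pooled variance. It has no bearing on detection of adverse events.

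**Observation by period**

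| Period | Discharged at 6 h | Admitted at 6 h |
|---|---|---|
| 0-6 h | ED monitoring plus Holter | the same |
| 6-24 h | Holter | Holter, hospital stay, continuous ECG until cardioversion |
| 24 h | on-site assessment | the same |
| 30 days | telephone assessment | the same |

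The scheduled difference is confined to the 6-24 h row. Within it, rhythm events can be read from the Holter in every patient, so the exposed part is non-ECG and non-serious events.

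**Inputs for an illustration**
- *h*, share at home after 6 h: 0.65 flecainide, 0.23 amiodarone. These are the 4-h conversion rates in section 3.4, used because no 6-h rate is given. Adverse events also block discharge, so a conversion rate is an upper bound for the discharge share at the same time point.
- *q*, true 6-24 h risk of exposed events, set equal in both arms: 10%, range 5% to 20%. Assumed.
- *d*, detection at home relative to hospital: 0.5 to 1. Assumed; the documents give no value.

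**Formula.** Observed risk = q × (h × d + 1 − h). The difference, flecainide minus amiodarone, reduces to −q × (h_F − h_A) × (1 − d), here −q × 0.42 × (1 − d).

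**Results at q = 10%**

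| d | Flecainide | Amiodarone | Difference (points) | Ratio |
|---|---|---|---|---|
| 1.0 | 10.00% | 10.00% | 0.0 | 1.00 |
| 0.9 | 9.35% | 9.77% | −0.4 | 0.96 |
| 0.7 | 8.05% | 9.31% | −1.3 | 0.86 |
| 0.5 | 6.75% | 8.85% | −2.1 | 0.76 |

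Check at d = 0.5 by counting missed events: flecainide 0.65 × 10% × 0.5 = 3.25 points; amiodarone 0.23 × 10% × 0.5 = 1.15 points; gap 2.10.

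**Sensitivity**
- Other risks at d = 0.5: q = 5% gives −0.05 × 0.42 × 0.5 = −1.05 points; q = 20% gives −4.2 points (13.5% versus 17.7%).
- Smaller gap in home shares, 65% versus 45%, q = 10%: −0.2 points at d = 0.9 and −1.0 at d = 0.5.
- Equal home shares: zero.
- With 100 per arm, q = 10% and d = 0.5, the artefact alone would give a significant result in flecainide's favour with probability about 0.08, against 0.025 with no artefact. It shifts the reported frequencies more than it produces false significance.

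**The case against.** The strongest case against has five parts.

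1. *The main safety endpoint is not touched.* The primary safety composite covers 0-6 h, when both arms are in the ED under the same observation. This stands. A reader might infer that the safety non-inferiority objective is itself biased; the documents do not support that.
2. *Most of the 30 days is observed alike.* The 24-h visit, the 30-day call and the instruction to report symptoms apply to everyone. This stands too: the unequal stretch is about 18 of the first 24 hours. But asymptomatic hypotension at home cannot be recovered by questions at a later visit, and events elicited at 24 h may still reflect what was noticed in hospital.
3. *Arrhythmias are protected.* All patients wear the Holter to 24 h, and section 3.1 gives arrhythmia detection as its purpose. This stands provided the Holter is the source. Table 3 names it for 24-h cardioversion but not for the 24-h arrhythmia outcome.
4. *Bias toward flecainide is not shown.* It needs poorer detection at home, which the documents do not quantify. Flecainide failures are admitted and given amiodarone, so their later events may count against flecainide, and the amiodarone infusion can run to 24 h, so true risks after 6 h need not be equal. This stands for the net direction. These are treatment effects, however, and cannot be relied on to cancel unequal detection.
5. *Tabulation by window may be in an analysis plan that is not shown.* That is fair, and the absence of such tables is not the point. The point is that the article sets one time frame across periods in which it also states that observation differs by outcome.

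**Conclusion.** The concern holds in a limited form. The 0 h to 30-day adverse-event frequency is liable to differential ascertainment of non-ECG and non-serious events between 6 h and about 24 h. Detection alone would favour the arm with more discharges, expected to be flecainide. The illustrative size is −0.4 to −2.1 points at an assumed 10% risk, zero if detection at home equals that in hospital, and larger only under higher assumed risk or poorer detection. None of these figures is established by the documents.

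It would go too far to say that the whole 30-day comparison is biased toward flecainide, or to apply the ratios above to every event after 6 h. They concern only events whose detection depends on setting. This is a modest weakness in one secondary outcome, worth correcting because the remedy uses data the trial already collects.

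**What to change.** Keep the full 30-day adverse-event outcome, and add the following to sections 3.7 and 3.8 and Table 3:

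- Present adverse events by window as well: 0-6 h, 6-24 h, and 24 h to 30 days.
- Name 0-6 h as the like-for-like comparison for all adverse events.
- State that 6-24 h arrhythmias come from the Holter worn by every patient and not from inpatient telemetry.
- Add a sensitivity comparison after 6 h limited to serious events and events elicited at the common 24-h visit and 30-day call.
- Record in the CRF where and how each event was detected. Recruitment is under way and this may be hard to reconstruct later.

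The cost is a few more tables and one CRF field. No event leaves the main comparison, and clinical management does not change. The sensitivity comparison omits some real inpatient events, such as hypotension during infusion, so it should accompany the full outcome and not replace it.

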## Data Availability

Data available on request due to privacy and ethical restrictions.

## Abbreviations

ED: Emergency Department, NOAC: Novel Oral Anticoagulation agents, PAF: Paroxysmal Atrial Fibrilation, PVC: Premature Ventricular Contraction, SVT: Sustained Ventricular Tachycardia, NSVT: Non-Sustained Ventricular Tachycardia, SHD: Structural Heart Disease, AE: Adverse Event, CRF: Case Report Form, AV: Atrioventricular, MI: Myocardial Infarction, EF: Ejection Fraction.
